### Aims and hypotheses

The key aims of the study are to:

1. Describe *transitions *in employment participation following a primary diagnosis of colorectal cancer within a 12-month period compared to individuals without cancer;

2. Identify the key factors influencing *work participation *during or after cancer treatment compared to individuals without cancer;

3. Identify the key factors influencing *time to work re-entry *after cancer treatment among individuals taking work leave for their cancer treatment;

4. Investigate the influence of changes in employment participation over a 12-month period on *HRQoL *at time 2 among individuals with cancer compared to those without cancer; and

5. Quantify the extent of *physical and cognitive limitations *at work (work disability) in individuals following a primary diagnosis of colorectal cancer.

We hypothesise that:

1. The proportion of middle-aged working adults with a primary diagnosis of colorectal cancer who substantially alter their work hours (i.e. by ≥20%) or stop working by 12 months after diagnosis will be more than 15% higher than among middle-aged working adults in the general community;

2. The key barriers to work participation or timely work re-entry after cancer will include regional or metastatic cancer at diagnosis, age, fatigue at six months, adjuvant therapy, living with an employed partner, limited work autonomy and low income; and,

3. Study participants who substantially reduce their work hours or leave the work force against their choice, will have clinically lower HRQoL scores at 12 months compared to those who remain employed at 12 months.

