### Sample size

Based on cancer incidence [16] and labour figures [17] it is anticipated that at least 522 working persons with colorectal cancer will be eligible annually. Sample size calculations were based on the number required to detect a 15% difference in work participation between workers with and without cancer assuming a 5% significance level and 80% power. Based on our past experience of recruiting colorectal cancer patients through the QCR and allowing for 85% doctors consent, 70% participant consent, 90% baseline interview completions and 75% retention at 12 months post-diagnosis, we will require initial contact with 258 patients with colorectal cancer to retain 125 patients at 12 months. The wave-on-wave attrition rates among continuing HILDA respondents have been consistently low, approximately 5% each year [18]. Data for 2,590 employed persons enrolled in HILDA aged 45-64 years Australia-wide will be available. HILDA data will be randomly matched 2:1 to patients with colorectal cancer, by gender and 5-year age category. Thus the total sample size to be selected for the study will be approximately 780.

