### Analyses

All analyses will include gender as a factor and will test for interactions of gender with other factors in the model. Gender differences are important, as not only do men and women have different work participation rates, work hours and occupation types in the general population [17], they respond and adjust differently to illnesses, have different health behaviours and other risk factors for cancer [24]. Where no effect modification is observed, pooled results will be presented. Socio-demographic characteristics will be compared at baseline to identify any statistically significant differences between the cancer and comparison groups. Descriptive analyses will be conducted to chart employment transitions over the year since diagnosis among the cancer group and over 2009-2010 year period among the comparison group. Although the first time point for the cancer group is six months after diagnosis, participants are asked to recall work circumstances (occupation type, hours worked, industry etc) at the time of diagnosis (retrospectively) and at time 1 (six months after diagnosis). Separate multivariable logistic regression modelling will identify explanatory variables that are significantly associated with work participation in the cancer and comparison groups. For these models, adjusted odds ratios with 95% confidence intervals and p-values will be computed. Cox proportional hazards models will assess time to work resumption in the participants with cancer and significant correlates of timely work re-entry. Mixed-effects modelling for the cancer group will be used to examine change in HRQoL scores (time 1 - time 2) by participants who reduce or leave in that time versus those who do not. We will also compare HRQoL scores between the cancer and comparison groups at time 2. Data on work limitations measured in the cancer group will be scored across the four domains and mixed-effects modelling undertaken to assess changes in scores between time 1 and time 2. Reasons for study withdrawal in the cancer sample will be closely monitored. Descriptive analyses of baseline variables for the 'completers' and 'non-completers' will identify any possible bias and the source and, if necessary, subsequent analyses will be weighted accordingly. In the comparison group, only responders at both HILDA Waves 9 and 10 will be included.

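### For work participation the plan names no between-group test or model, so hypothesis 1 gets at most a crude difference and the comparison in aim 2 gets no valid test

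*Protocol article*

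**What the plan says.** **The question (Protocol article, Aims and hypotheses).** Aim 1 describes employment transitions "within a 12-month period compared to individuals without cancer". Aim 2, on factors influencing work participation, carries the same comparison. Hypothesis 1 is a difference in proportions: those with cancer who change their hours by at least 20% or stop work by 12 months "will be more than 15% higher than among middle-aged working adults in the general community".

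**The sample size (Sample size).** The study is sized to "detect a 15% difference in work participation between workers with and without cancer", "assuming a 5% significance level and 80% power". On the design, "HILDA data will be randomly matched 2:1 to patients with colorectal cancer, by gender and 5-year age category".

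**The analysis of work participation (Analyses).** First, "Descriptive analyses will be conducted to chart employment transitions over the year since diagnosis among the cancer group"; the same sentence covers the comparison group over 2009-2010. Second, "Separate multivariable logistic regression modelling will identify explanatory variables that are significantly associated with work participation in the cancer and comparison groups". Adjusted odds ratios, 95% confidence intervals and p-values are promised for these models.

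**Between-group comparisons that are stated.** The Analyses section compares baseline socio-demographic characteristics between the groups, and HRQoL scores at time 2. Note a to Table 1 says that key work questions will be compared across the groups over a common year, without giving a method.

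**The concern.** In a model fitted only to cancer cases, or only to comparators, cancer status is constant. Its odds ratios describe the factors within that group, and none of them is the effect of cancer. The only route to hypothesis 1 is then to subtract two charted proportions, with no stated interval or test and no adjustment beyond matching on gender and 5-year age group. Cases are Queensland residents and comparators come from all of Australia. The plan looks for baseline differences but names no model of work participation in which they could adjust the contrast.

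For aim 2, two separate lists of significant factors invite a side-by-side reading. A factor that reaches significance in one group and not in the other has not been shown to act differently.

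What is at stake is the study's lead hypothesis and its stated advance. The Background faults an earlier colorectal cohort for having no comparison group, and the Discussion presents this study as overcoming that limitation.

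**Working it through.** **1. Question against stated analysis, for work participation**

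| Item | Contrast required | Analysis stated |
|---|---|---|
| Hypothesis 1 | Difference in proportions between groups | Charted in each group; no test, interval or adjustment |
| Aim 1 | Transitions compared with no cancer | Charted in each group |
| Aim 2 | Factors compared with no cancer | One logistic model per group; no interaction with group |
| Sample size | 15% between-group difference | No matching test or model named |

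The Cox, HRQoL-change and work-limitation models are for the cancer group. The two-stage probit approach concerns health status and work, and names no group contrast. The only interactions named are with gender.

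**2. The plan's own sample size.** The plan gives the difference (15%, taken here as percentage points), 5% significance, 80% power and 2:1 matching. It gives neither base rates nor sidedness, so a two-sided test is assumed. The standard two-proportion formula at 2:1 then needs these numbers of cases:
- 5% vs 20%: 52
- 20% vs 35%: 101
- 35% vs 50%: 126
- 40% vs 55%: 130, the largest over base rates of 5% to 50%

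So 125 retained cases fit a two-group comparison of proportions near 35% vs 50%. That is the analysis the Analyses section does not name.

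The recruitment chain, "allowing for 85% doctors consent, 70% participant consent, 90% baseline interview completions and 75% retention at 12 months post-diagnosis", gives 0.85 × 0.70 × 0.90 × 0.75 = 0.4016. Then 258 × 0.4016 = 103.6 retained, not 125. That is a separate matter, but power is shown for 104 as well.

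**3. Can the data carry the missing test?** Power = Φ{[Δ − 1.96√(p̄q̄(1/n₁ + 1/n₂))] / √(p₁q₁/n₁ + p₂q₂/n₂)}. For 35% vs 20% with 125 and 250:
- p̄ = (125 × 0.35 + 250 × 0.20)/375 = 0.25
- null SE = √(0.25 × 0.75 × 0.012) = 0.0474
- alternative SE = √(0.00182 + 0.00064) = 0.0496
- power = Φ[(0.15 − 0.0930)/0.0496] = Φ(1.15) = 87.5%

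Over assumed comparison-group rates of 5% to 50%:

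| Cases vs comparators | Power for 15 points |
|---|---|
| 125 vs 250 | 79% to 99% |
| 104 vs 208 | 71% to 97% |
| 104 vs 520 | 81% to 99% |

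**4. What reading separate models side by side would do.** This is an illustration, and its inputs are assumptions. A factor has 50% prevalence and the same odds ratio of 2 in both groups. The outcome occurs in 36% of 125 cases and 21% of 250 comparators. The 36% is near the pooled proportion not working in the cohort cited in the Background, (0.33 × 621 + 0.40 × 354)/975 = 35.5%; the 21% is 15 points lower.
- Cancer model: SE(log OR) = 1/√(125 × 0.25 × 0.36 × 0.64) = 0.373; power = Φ(0.693/0.373 − 1.96) = 46%
- Comparison model: SE = 1/√(250 × 0.25 × 0.21 × 0.79) = 0.311; power = Φ(0.693/0.311 − 1.96) = 61%
- Significant in exactly one group: 0.46 × 0.39 + 0.54 × 0.61 = 51%, with no true difference

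The same formulas with an odds ratio of 1.5 give powers of 19% and 26%, and 35% discordance. With an odds ratio of 3 they give 84% and 94%, and 20% discordance.

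**5. Power of the proper test for aim 2.** The SE of the interaction is √(0.373² + 0.311²) = 0.485. If the odds ratio in one group were truly twice that in the other, power would be about Φ(0.693/0.485 − 1.96) = 30%.

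**The case against.** The strongest defence is that a condensed article need not name every test. The study is sized on a between-group difference, the Table 1 note says that work questions will be compared, and a fuller plan may supply the method. Aim 1 asks only for a description, which charting provides. Transitions are charted in both groups, with identical work items and matching on gender and age, so the two proportions behind hypothesis 1 will be available. Stage, adjuvant therapy and fatigue have meaning only among cases, so some separate modelling is right.

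Much of this stands. A reader might infer that the study has no between-group analysis at all; the planned HRQoL comparison at time 2 contradicts that. A reader might also infer that hypothesis 1 and the comparative aims cannot be answered. The documents do not support that either, since the data permit a crude difference and an adequately powered test. Nor does the plan say that significance patterns will be compared across the two models, so the 51% shows a risk, not a stated procedure. The documents do not establish that the groups differ in occupation or income.

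What does not stand is treating this as mere omission. The article chooses an analysis for this outcome, and that choice does not fit the hypothesis. The same section names between-group comparisons for baseline characteristics and HRQoL, and interactions for gender. A later plan that followed it would carry the mismatch forward.

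**Conclusion.** The point holds, limited to work participation. No between-group test, group term or group-by-factor interaction is specified for the outcome of hypothesis 1, which is also the basis of the sample size. The analyses as written give at most a crude, unadjusted difference for hypothesis 1, and no valid test of the comparative part of aim 2. Aim 1, as a description, is largely served.

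This is a correctable mismatch, not a loss of information. The power figures rest on assumed base rates, a two-sided 5% test, an absolute reading of the 15%, and no allowance for covariates or for the matching. The discordance figures (20% to 51% over odds ratios of 1.5 to 3) rest on assumed inputs and on a reading across models that the plan does not state. The conclusion depends on neither. It follows from setting the hypothesis beside the stated models. It does take the separate models to mean one per group, which is the natural reading; if something else was meant, the sentence needs rewording.

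**What to change.** Add one pooled logistic model of the 12-month work outcome defined in hypothesis 1 (hours changed by at least 20%, or stopped work). Include a cancer indicator, the matching factors (gender and 5-year age group) and pre-specified baseline covariates collected in both groups, such as education, occupation and baseline hours. Report the adjusted risk difference and odds ratio, each with a 95% CI, as the hypothesis 1 result, with the crude difference beside it.

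For aim 2, test group-by-factor interactions in this model for a short, pre-specified list of factors, and draw no conclusion from significance in one group alone. Keep a cancer-only model for the clinical predictors (stage, adjuvant therapy, fatigue).

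Do not adjust for state. Every case is a Queensland resident, so the adjusted contrast would rest on Queensland comparators alone. A sensitivity analysis restricted to Queensland comparators makes that restriction explicit.

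The cost is revised wording in the analysis plan and a little more analysis, with no new data collection. The drawback is low power for the interactions (about 30% in the illustration above), so they should be reported as estimates with intervals.

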**Methods/Design:**

An observational population-based study has been designed involving 260 adults newly-diagnosed with colorectal cancer between January 2010 and September 2011 and who were in paid employment at the time they were diagnosed. These cancer cases will be compared to a nationally representative comparison group of 520 adults with no history of cancer from the general population. Eligible cases will have a histologically confirmed diagnosis of colorectal cancer and will be identified through the Queensland Cancer Registry. Data on the comparison group will be drawn from the Household, Income and Labour Dynamics in Australia (HILDA) Survey. Data collection for the cancer group will occur at 6 and 12 months after diagnosis, with work questions also asked about the time of diagnosis, while retrospective data on the comparison group will be come from HILDA Waves 2009 and 2010. Using validated instruments administered via telephone and postal surveys, data will be collected on socio-demographic factors, work status and circumstances, and health-related quality of life (HRQoL) for both groups while the cases will have additional data collected on cancer treatment and symptoms, work productivity and cancer-related HRQoL. Primary outcomes include change in work participation at 12 months, time to work re-entry, work limitations and change in HRQoL status.

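### Hypothesis 3 concerns HRQoL at 12 months by work change since diagnosis, but the only work-change analysis described uses the 6-to-12-month change in HRQoL, so no described analysis makes that contrast

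*Protocol article*

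**What the plan says.** **The question.** In the protocol article, Aims and hypotheses, aim 4 is to "Investigate the influence of changes in employment participation over a 12-month period on" quality of life. The outcome in that aim is taken "at time 2 among individuals with cancer compared to those without cancer". Hypothesis 3 predicts that participants who substantially cut their hours, or leave work involuntarily, "will have clinically lower HRQoL scores at 12 months compared to those who remain employed at 12 months". Both name a score at 12 months.

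**The outcome list.** The abstract, under Methods/Design, states: "Primary outcomes include change in work participation at 12 months, time to work re-entry, work limitations and change in HRQoL status". It gives no time window for the HRQoL change.

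**The analysis.** Under Analyses: "Mixed-effects modelling for the cancer group will be used to examine change in HRQoL scores (time 1 - time 2"), compared "by participants who reduce or leave in that time versus those who do not". The next sentence adds: "We will also compare HRQoL scores between the cancer and comparison groups at time 2".

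**The timing.** Table 1 and the section on telephone interviews put time 1 for cases at six months after diagnosis and time 2 at 12 months. Footnote a to Table 1 takes cases back to diagnosis by recall, but for work questions only.

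**The concern.** The question and the analysis differ in two respects: the HRQoL quantity (level at 12 months against change from month 6) and the period over which work change is counted (12 months against the last six). The only time-2 comparison described is cases against the HILDA group. That covers part of aim 4, but it does not separate people whose work changed from those whose work did not.

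What is at stake is the reading of a listed primary outcome. Someone who left work in month 2 and has poor HRQoL at both interviews supports hypothesis 3, yet shows no change between time 1 and time 2. If many participants who change their work do so early, during treatment, the planned contrast could be near zero, or could describe late leavers only. It might then be reported as evidence on hypothesis 3.

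**Working it through.** The plan gives no HRQoL sample-size or power figure to reproduce; its only calculation is for work participation. The check is therefore a comparison of the text, then algebra, then an illustration.

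**1. The two specifications side by side**

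| | Aim 4 and hypothesis 3 | Work-change model in Analyses |
|---|---|---|
| HRQoL quantity | score at 12 months | change between 6 and 12 months |
| Work-change window | 12 months (aim 4) | between time 1 and time 2 |
| Reference group | employed at 12 months | everyone who did not reduce or leave in that window |

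Taken literally, the right-hand reference group includes people who had already stopped before month 6. The text does not exclude them.

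**2. Algebra**

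Let D6 and D12 be the mean HRQoL differences (exposed minus reference) at 6 and 12 months. The difference in change is D12 − D6; writing it as time 1 − time 2 only reverses the sign. If the deficit is d at both times, the 12-month contrast is −d and the change contrast is −d − (−d) = 0.

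**3. Early and late leavers**

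Assume 25% leave before month 6, 10% leave between months 6 and 12, and leaving lowers HRQoL by 0.5 SD from then on.

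- All 35% exposed, 12-month level: −0.50 SD.
- All 35% exposed, change: only the late leavers change, so −0.50 × 10/35 = −0.14 SD.
- Literal grouping, change: late leavers −0.50, everyone else 0, so −0.50 SD. This concerns the late 10% only.
- Literal grouping, 12-month level: the reference mean is −0.50 × 25/90 = −0.14, so the contrast is −0.50 + 0.14 = −0.36 SD.

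A simulation with the same inputs gave −0.50, −0.14, −0.50 and −0.36. The early leavers' effect is diluted in the second line, absent from the third, and biases the reference group in the fourth. Only the first line estimates the 12-month effect in everyone who left.

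**4. Power (illustration)**

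Inputs: 125 cases retained at 12 months (Sample size section). The share exposed is assumed to be 35–40%, guided by the 33% of men and 40% of women not working at 12 months in the earlier cohort cited in the Background. Also assumed: SD 1, a 12-month deficit of 0.5, a 6-to-12-month correlation ρ of 0.5–0.7, and two-sided 5% with a normal approximation.

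- SE of the level difference = √(1/n1 + 1/n0). At 35%: √(1/43.75 + 1/81.25) = 0.188. At 40%: √(1/50 + 1/75) = 0.183.
- Level power = Φ(0.5/SE − 1.96) = Φ(0.71) = 76% and Φ(0.78) = 78%.
- SE of the change difference = level SE × √(2(1 − ρ)), a factor of 1.00, 0.89 or 0.77 for ρ = 0.5, 0.6 or 0.7.

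| Share of the deficit arising after month 6 | Change contrast | Power of the change test |
|---|---|---|
| all | 0.50 SD | 76–94% |
| half | 0.25 SD | 27–42% |
| none | 0 | 2.5% in the expected direction (5% two-sided) |

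The table takes the exposed group as everyone whose work changed since diagnosis. The plan's own participation rates give 258 × 0.85 × 0.70 × 0.90 × 0.75 = 104 retained cases, not 125. At 104 (36 against 68), level power is 68%. The pattern does not change.

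**The case against.** **A mixed model fitted to both time points can already give the 12-month group difference, and an article may leave the choice of contrast to the analysis plan.** The first part is correct and makes the fix cheap. The second would settle the matter if the article were silent. It is not: it names change as the quantity examined and confines the groups to the later window.

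**Under the grouping as written, change may be the better contrast.** This stands. If the exposed left after month 6, their six-month deficit came before leaving, and removing it takes out prior differences in health. In step 3 the change contrast recovers the full −0.50 SD for late leavers, while the level shrinks to −0.36 SD. A reader might infer that any six-month deficit hides a cost of leaving work. The text does not support that: cancellation of a work effect requires early leavers to be in the exposed group, and the literal wording does not put them there. The wording instead moves them into the reference group, so their effect still goes unestimated.

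**The simultaneous probit least squares model covers it.** That model complements the other analyses and treats health as endogenous to work participation. It does not state hypothesis 3's 12-month contrast.

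**The abstract does not contradict the aims outright.** This is fair, since its HRQoL change has no window. For cases, however, 6 to 12 months is the only HRQoL change available.

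**The magnitudes are assumed.** This also stands. The documents do not say how much of any HRQoL deficit is present by month 6.

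**Conclusion.** The mismatch is in the text and does not depend on any assumed figure. Aim 4 and hypothesis 3 concern HRQoL at 12 months with work change counted over the year, while the described model uses the 6-to-12-month change with work change counted over the same six months. No described analysis makes hypothesis 3's contrast, and the experience of people who stopped or cut back before month 6 is either cancelled or placed in the reference group.

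The size is conditional. With a 0.5 SD deficit and 125 cases, the loss ranges from nothing (all of the deficit arises after month 6) to the whole of the test's power (all of it present by then).

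Two stronger readings are tempting and should not be drawn. One is that level and change would give opposite answers: the illustration shows a deficit against a smaller or null difference, never a reversal. The other is that the study cannot test hypothesis 3: the planned data and model can, once the contrast and groups are stated.

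**What to change.** - For hypothesis 3 and the work-change part of aim 4, name the time-2 group contrast from the planned mixed model as the test.
- Define work change from diagnosis to 12 months, using the work data recalled at the six-month interview as baseline.
- Use groups that do not overlap. Someone who cuts hours is still employed, so hypothesis 3's two groups overlap as worded. Compare those who substantially reduced (hours cut by at least 20%, the threshold in hypothesis 1) or left involuntarily with those still employed without a substantial reduction. Say whether the involuntary condition also applies to reduced hours, and report voluntary leavers separately.
- Adjust for stage and treatment, both already collected.
- Keep the 6-to-12-month change as a secondary contrast, and say where people who stopped or cut back before month 6 are placed in it.
- Align the HRQoL entry in the abstract's primary-outcome list with this.

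The cost is wording plus one contrast from a model already planned; no further HRQoL measurement is needed. The downside is that the 12-month level is more open to confounding by disease severity than the change is. Adjustment reduces that without removing it, which is a reason to report both.

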### Data collection sources

Data will be collected during this project from four sources (Table 1):

**Table 1 T1:** Questionnaire item domains at each time point by cancer cases and general-population comparison group

	Cancer Group		Comparison Group
**Method**	**Telephone interview**	**Mailed questionnaire**	**Face-to-face interview**

Time 1^a^	1. Socio-demographics^b^ 2. Cancer treatments 3. Symptoms (MSAS^b^) 4. Work questions^a^ 5. Work limitations (WLQ)	6. Quality of life (SF-36)^b^ 7. Health behaviours & conditions^b^ 8. Cancer-specific quality of life (FACT-C) 9. Financial strain^b^	Question groups 1, 4, 6, 7, 8, 9 from HILDA Wave 9, 2009 data

Time 2	Repeat question groups 2-8		Question groups 1, 4, 6, 7, 8 from HILDA Wave 10, 2010 data

^a ^Time 1 for the Cancer Group occurs six-months after diagnosis however retrospective work questions are asked about their time of diagnosis (baseline) and about their current time (six months after diagnosis) therefore a common one year period will be compared across the cancer and comparison groups for key work questions.

^b^These questions are the same as those in the comparison group to enable direct comparison between groups.

Abbrevs: FACT-C = Functional Assessment in Cancer Therapy plus Colorectal Cancer module, HILDA = Household, Income and Labour Dynamics in Australia, MSAS = Memorial Symptom Assessment Scale, SF-36 = Medical Outcomes Study Short Form 36, WLQ = Work Limitations Questionnaire.

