#### 2) Telephone interviews (cancer group)

Participants with cancer will take part in structured telephone interviews at 6 and 12 months after diagnosis. At the 6-month data collection time point we will also ask participants to recall work-related information at the time they were diagnosed with cancer (baseline). Telephone interviews will be undertaken in order to maximise response rates, reach a wide geographical region and minimise participant burden, the latter being important in a working population that may require out-of-hours contact. Interviews will be conducted by trained and experienced interviewers. To minimise respondent burden, interviews will be kept to approximately 30 minutes each. A flexible interview schedule will be adopted and tailored to suit the schedules of working participants.

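### As written, the cancer-group HRQoL model counts work change only between months 6 and 12, so patients who stopped or cut hours earlier join its reference group, at odds with aim 4 and with hypothesis 3's reference group

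*Protocol article*

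**What the plan says.** The cancer-group HRQoL model is described once, in the Analyses section of the protocol article. Mixed-effects modelling will "examine change in HRQoL scores (time 1 - time 2) by participants who reduce or leave in that time versus those who do not".

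The time points are fixed elsewhere:

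- Footnote a to Table 1 (Data collection sources): "Time 1 for the Cancer Group occurs six-months after diagnosis". The Analyses section repeats this: "Although the first time point for the cancer group is six months after diagnosis".
- Telephone interviews (cancer group): "Participants with cancer will take part in structured telephone interviews at 6 and 12 months after diagnosis". Work at diagnosis, which the protocol calls baseline, is recalled at the six-month interview.
- Study participants: cases must have been in paid employment when diagnosed.

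The questions to be answered are in Aims and hypotheses. Aim 4 is to "Investigate the influence of changes in employment participation over a 12-month period on" HRQoL at time 2, in people with and without cancer. Hypothesis 3 expects that participants "who substantially reduce their work hours or leave the work force against their choice, will have clinically lower HRQoL scores at 12 months", and compares them with people still employed at that time. The abstract lists change in HRQoL status among the primary outcomes.

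**The concern.** The exposure in the HRQoL model is a work change between two interviews, the first of which takes place six months after diagnosis. Aim 3 itself expects some patients to take leave for treatment, so stopping before month 6 is an anticipated pattern. A patient who stopped then and stayed out has nothing left to change between the interviews. The rule offers two classes, and this patient falls into the unexposed one.

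At stake is a primary outcome. If the reference group holds people whose work was already disrupted, the contrast does not compare disrupted with undisrupted work, and a true difference in 12-month HRQoL may be understated.

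**Working it through.** The protocol gives no sample size, power or effect size for this comparison, so there is no figure to reproduce. The check compares definitions and then illustrates the possible size.

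**Step 1: the window.** The model sentence refers back to its own bracketed interval, time 1 to time 2. For cases that is month 6 to month 12.

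**Step 2: where patients fall.** All were employed at month 0.

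| Pattern | Class under the model sentence | Class by change from diagnosis to month 12 |
|---|---|---|
| Stopped before month 6, still off at 12 | did not reduce or leave | left |
| Cut hours by 20% or more before month 6, no further change | did not reduce or leave | reduced |
| Stopped before month 6, back at previous hours by 12 | did not reduce or leave | no substantial change |
| Unchanged at 6, reduced or left by 12 | reduced or left | reduced or left |
| Unchanged throughout | did not reduce or leave | no substantial change |

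The first two rows are misplaced. No stated rule excludes them or classes them separately.

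**Step 3: against the aims.**

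- Aim 4 spans 12 months; the model spans six. This conflict is direct.
- Hypothesis 3 has people employed at 12 months as its reference. The first row is not employed at 12 months, yet sits in the model's reference group.
- The second row shows that hypothesis 3 needs tightening too: someone who cut hours substantially but still works meets both its exposed and its reference description.
- The other HRQoL comparison in Analyses (cancer versus comparison group at time 2) is not stated by work change. The simultaneous probit and least-squares model does not redefine the work-change groups.

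**Step 4: illustration of size.** Inputs:

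- Not working at 12 months in the earlier Australian colorectal cohort (Background): 33% of 621 men and 40% of 354 women. Pooled p = (0.33 × 621 + 0.40 × 354) / 975 = 346.5 / 975 = 0.355.
- Patients retained at 12 months (Sample size): 125. Off work at 12 months: S = 125 × 0.355 = 44.4.
- Share f of these who stopped before month 6 and stayed out: not in the document; **assumed** 30% to 90%.

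Early stoppers e = f × S; late stoppers l = S − e; reference group as written R = 125 − l; contaminated share = e / R. Hours reducers are ignored.

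| f | e | l (exposed as written) | R | e / R |
|---|---|---|---|---|
| 30% | 13.3 | 31.1 | 93.9 | 14% |
| 50% | 22.2 | 22.2 | 102.8 | 22% |
| 70% | 31.1 | 13.3 | 111.7 | 28% |
| 90% | 40.0 | 4.4 | 120.6 | 33% |

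The share does not depend on reaching 125 patients: e / R = f·p / (1 − (1 − f)·p).

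If early and late stoppers had the same mean 12-month deficit, a 12-month level contrast would shrink by the factor 1 − e / R, that is to 0.86, 0.78, 0.72 or 0.67 of its true size. This does not carry over to the change score from month 6.

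**The case against.** **The wording may be loose.** The same section charts employment transitions across the whole year from diagnosis, and footnote a to Table 1 sets a shared one-year period for the key work questions. The authors may have meant the year. But the footnote concerns the comparison between cancer and comparison groups, the protocol keeps baseline and time 1 apart, and the model sentence names its interval. If the year was meant, the sentence still needs correcting.

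**Matching the two windows is defensible.** HRQoL is first measured at month 6, so relating HRQoL change to work change over the same six months is a coherent within-person analysis, and the abstract names HRQoL change as an outcome. This stands, and is why the model should be kept. It does not justify placing early stoppers among the unaffected.

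**Hypothesis 3 is not shown to be untestable.** A reader might infer that the plan contradicts hypothesis 3 throughout and leaves it untested. The text does not support that. The hypothesis gives no start for its window, and a mixed model on both time points can yield 12-month means. The conflict lies in the reference group, and those means would still be formed on the wrong grouping.

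**Involuntary change.** A reader might also object that the model sentence omits whether the change was against the patient's choice. That is exposure detail which an article may leave to the full plan.

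**Direction.** A reversed sign, through early stoppers recovering between months 6 and 12, is conceivable, but nothing in the document supports predicting it.

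**Conclusion.** The point holds as a conflict between a stated rule and the protocol's own aim 4 and hypothesis 3 reference group. Taken literally, the rule places patients whose work changed before month 6 in the reference group, and no other stated HRQoL analysis is defined by work change.

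The size is unknown. The range of about 14% to 33% of the reference group rests on the earlier cohort's stopping rates, an assumed 30% to 90% early-stopping share, and no return to work by month 12. It omits hours reducers on both sides, so it should not be read as the loss in the planned analysis. Dilution of a 12-month difference is likely; the effect on the month 6 to 12 change contrast could differ in size or direction.

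**What to change.** - For hypothesis 3 and aim 4, define work change from recalled status and hours at diagnosis to month 12, applying the 20% threshold of hypothesis 1 to reductions. Use as reference those still employed at 12 months without substantial reduction.
- Report time-2 HRQoL by these groups. For aim 4, apply the same 12-month classification in the comparison group, whose two survey waves are a year apart.
- Keep the month 6 to 12 mixed model as complementary, with patients already stopped or reduced by month 6 as a separate category.

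The work items and SF-36 needed are already planned, so the cost is a change of wording and one more category. Splitting leavers into wanted and unwanted exits by preferred hours is not part of this fix: the article lists no item on the reason for leaving work, and feasibility in people with no current hours is not shown.

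The downside is that HRQoL is not measured at diagnosis. The 12-month contrast is cross-sectional, needs adjustment for stage and comorbidity, and stays open to poor health causing work exit, the endogeneity that the protocol itself raises. Whether also to adjust for time-1 HRQoL is debatable, and the authors should state their choice.
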